## Abstract

**Background:**

Smoking is an important risk factor for mental health-related problems. Numerous studies have supported a bi-directional association between cigarette smoking and depression. Despite the advances in understanding the comorbidity between both problems, the most effective psychological treatment that simultaneously targets smoking and depressive symptomatology remains unclear. The objective of this study is to assess the effectiveness of a cognitive-behavioral intervention for smoking cessation with components of behavioral activation for managing depressed mood.

**Method:**

A single blind, three-arm, superiority randomized controlled trial is proposed. Participants will be smokers over 18 years old, who smoke at least 8 cigarettes per day. Participants will be randomized to one of three conditions, using a 2:2:1 allocation ratio: 1) standard cognitive-behavioral smoking cessation treatment; 2) standard cognitive-behavioral smoking cessation treatment plus behavioral activation; or 3) a three-month delayed treatment control group. The primary outcome measures will be biochemically verified point-prevalence abstinence (carbon monoxide in expired air) and significant change from baseline in depressive symptoms to the end of treatment, and at the 3-, 6-, and 12-month follow-up.

**Discussion:**

This study aims to assess the efficacy of a cognitive-behavioral intervention with behavioral activation components for smoking cessation and depressive symptoms, compared to a standard cognitive-behavioral intervention to quit smoking. As the relation between depressive symptoms, even at subclinical levels, and quitting smoking difficulties is well known, we expect that such intervention will allow obtaining higher abstinence rates, lower relapse rates, and mood improvement.

**Trial registration:**

ClinicalTrials.gov: NCT02844595. Retrospectively registered 19th July, 2016. The study started in January 2016, and the recruitment is ongoing.

## Background

Both smoking and depression are leading causes of disability, mortality, and morbidity worldwide [1–3]. The frequent co-occurrence of depression and smoking is well documented, and empirical work suggests that smoking-depression relations could be bi-directional [4, 5]. Epidemiological research have shown that mood disorders are more prevalent among smokers compared to nonsmokers from the general population [6–8], and it has been found that smoking is also associated with a greater risk of onset and persistence of depression [9]. In addition, among treatment-seeking smokers, several studies have found greater levels of mood disorders, in both lifetime and past-year diagnoses [10].

Evidence suggests that smokers from the general population with depressive symptoms or with a depressive disorder, compared to those without one, present higher levels of cigarette consumption, greater nicotine dependence, are more likely to suffer intense nicotine withdrawal symptoms and to fail when trying to quit smoking, have more difficulties to maintain abstinence, and have a higher risk of smoking relapse over time [5, 11–13]. Additionally, it has been shown that even very low levels of pretreatment depressive symptoms can impact smoking cessation treatment outcomes [14].

At the same time, studies conducted both in general and clinical populations have found that smoking cessation is related to mood improvement in people who are able to remain abstinent [15–17]. In a recent meta-analysis that included 26 studies assessing mental health in persons with and without psychiatric disorders, Taylor and colleagues [18] found that quitting smoking is associated with a decrease in depressive and anxiety symptoms, with a reduction in stress levels, and an improvement in quality of life.

The U.S. Preventive Services Task Force (USPSTF) found strong evidence that behavioral interventions substantially improve achievement of tobacco cessation [19]. Despite this, a reduction over time in abstinence rates has been shown following psychological and/or pharmacological smoking cessation treatment [20–22]. As recent studies suggest, this trend could be due to a change in treatment-seeking smokers, who show significantly greater self-reported depressive symptoms when compared to prior studies [20, 23].

In relation to the efficacy of smoking cessation treatments aimed at smokers with depression, Gierisch and colleagues [24] conducted a systematic review and meta-analysis of studies examining smoking cessation interventions for smokers with past or current depression. Their results showed a positive effect of adding a behavioral mood management component to smoking cessation intervention. Recently, van der Meer and colleagues [25] reviewed 33 trials that included smoking cessation interventions with specific mood management components. Their results, in line with previous ones, showed a significant positive effect of adding psychosocial mood management components to a standard smoking cessation intervention in smokers with current or past depression.

Behavioral activation (BA) may be considered as a parsimonious treatment option for depression, because it is less complex but just as effective as cognitive-behavioral therapy and anti-depressant medication [26, 27]. Moreover, Richards and colleagues [28], who conducted the largest trial of BA for depression to date, found that BA therapy is more time-efficient and cost-effective when compared to cognitive-behavioral treatment for depression, suggesting that BA should be a front-line treatment for depression. It consists of a structured intervention that uses the principles of operant conditioning to activate clients to increase rewarding experiences in their lives, the enjoyment of daily activities, and to reconnect with environmental positive reinforcement [29].

The central role of reinforcement in the BA approach makes this intervention a good option to be included in an intervention to quit smoking. Audrain-McGovern and colleagues [30] found that when depression-prone smokers quit smoking, they experience the loss of smoking reinforcement, a diminution in positive mood, a reduction in the pleasure obtained from other rewarding experiences, and an increase in negative affect. Their results also suggest that a smoking lapse could reestablish these affective and reward-related functions, resulting in a high probability of smoking relapse.

In fact, BA integrated in smoking cessation intervention has shown preliminary efficacy for depressive symptoms and improving smoking cessation outcomes among adult smokers with depression. MacPherson and colleagues [31] carried out a pilot study [*N* = 68] examining whether a behavioral activation treatment for smoking cessation (BATS) could improve abstinence rates and depressive symptoms compared to a standard smoking cessation treatment. They found that the BATS group had greater likelihood of point prevalence abstinence and lower depressive symptoms at the end of the treatment and at 6-month follow-up, compared with the standard smoking cessation treatment group. Also, a recent case series study [32] conducted with 3 inpatients (who participated in the open-label pilot phase of a larger ongoing RCT) at a substance use treatment center, found that the BA-Enhancing Smoking Cessation Program provides good smoking cessation results and important decreases in depressive symptoms.

Taken together, these previous findings suggest a potential benefit of adding BA components to a smoking cessation treatment. Through this intervention approach, exposure to positive reinforcing alternatives to smoking cigarettes would be increased, and the distress of the withdrawal syndrome could be reduced, resulting in a possible improvement of smoking abstinence rates and mood, even in smokers with lower depressive symptoms. Due to the novelty of this smoking cessation intervention, further research is needed with controlled trial designs, larger samples, and longer follow-up periods.

## Aims

The main aims of the present randomized controlled trial are: 1) to assess the efficacy (smoking abstinence rates) of a cognitive-behavioral smoking cessation treatment with elements from behavioral activation for managing depressed mood, compared with a standard smoking cessation treatment, at the end of treatment, and at 3-, 6-, and 12-month follow-ups; and 2) to assess whether the applied cognitive-behavioral smoking cessation treatment plus behavioral activation improves depressed mood, compared with a standard smoking cessation treatment, at the end of treatment and at 3-, 6-, and 12-month follow-ups.

## Method

### Study design

A three-arm, single blind superiority randomized controlled design is proposed to assess the effectiveness of a cognitive-behavioral intervention for smoking cessation with components of BA. The overall study design is summarized in Fig. 1.

**Fig. 1 Fig1:**
[figure not shown]
Consort Diagram of Trial Progression

### Recruitment

Participants will be recruited through the media, posters in healthcare centers, word of mouth, or they will be referred to the unit by their primary care physician or other specialized services of the healthcare system. The different phases of the study (assessment, treatment, and follow-ups) will be carried out at the Smoking Cessation and Addictive Disorders Unit of the University of Santiago de Compostela, Galicia (Spain). Before participants enroll in the study, informed consent for participation will be obtained.

### Target population, blinding, randomization, and procedure

Sample selection will be carried out according to the following inclusion criteria: aged 18 or over; wishing to participate in the treatment program; providing written informed consent; and smoking 8 or more cigarettes per day. Exclusion criteria will be: a diagnosis of severe mental disorder (bipolar disorder and/or psychotic disorder); concurrent substance use disorder (alcohol, cannabis, stimulant, hallucinogen and/or opioid); having participated in the same or similar treatment over the previous year or having received pharmacological smoking cessation treatment (nicotine replacement therapy, bupropion, or varenicline) over the previous year; presence of a high life-risk pathology that would require immediate individual intervention (i.e., recent myocardial infarction); smoking tobacco products other than cigarettes (i.e., cigars); or failing to attend the first treatment session.

Two baseline assessment sessions will be carried out in a face-to-face interview. Researchers conducting such assessments will be blind to group allocation, which will occur subsequently. Due to the nature of the study, participants will be aware that they will be assigned to one of the three arms.

The randomization will be conducted according to a computer generated allocation sequence (ratio: 2.2.1.): (1) standard cognitive-behavioral smoking cessation treatment; (2) standard cognitive-behavioral smoking cessation treatment plus behavioral activation; or (3) a 3-month delayed treatment control group. After that, both active treatments will be administered in eight weekly 60-min sessions.

At the end of treatment, there will be a post-treatment assessment (during session 8) and face-to-face follow-ups at 3, 6, and 12 months (Fig. 1). Self-reported abstinence at the end of treatment and at the follow-ups will be corroborated by measures of CO in expired air. In those cases in which it is not possible to locate the participants, they will be considered to be smokers, and at the same level (in terms of tobacco-related variables) as at the baseline assessment.

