#### Treatment delayed control group

It will be a delayed-treatment control group for a period of 3 months. After the 3-month period, another assessment will be carried out, and then participants will be offered to participate in a smoking cessation treatment (Table 2).

**Table 2 Tab2:** Summary of session-by-session outline of intervention procedures

Ss	Cognitive-behavioral Smoking Cessation Treatment (CBSCT)	CBSCT + Behavioral Activation
1	Overview of treatment Smoking cessation treatment rationale Review self-monitoring (tracking cigarettes and smoking antecedents and consequences) Indications about how to graphically represent the No. of cigarettes/day Reasons for smoking and for quitting Discuss smoking history and quit experiences Explain and provide written materials about tobacco, nicotine dependence, smoking health consequences and quit smoking benefits Explain nicotine fading through brand change Physiological feedback (CO) As homework: - Brand change - Communicate to at least one person [family, friend, coworker, etc.) that he/she is trying to quit smoking in the next 30 days - Not smoke more cigarettes than the average of those smoked the previous week - Leave a third of the cigarette without smoking - Refuse cigarette offers	Overview of treatment Smoking cessation treatment rationale Review self-monitoring (tracking cigarettes and smoking antecedents and consequences) Indications about how to graphically represent the No. of cigarettes/day Reasons for smoking and for quitting Discuss smoking history and quit experiences Explain and provide written materials about tobacco, nicotine dependence, smoking health consequences and quit smoking benefits Explain nicotine fading through brand change Physiological feedback (CO) As homework: - Brand change - Communicate to at least one person (family, friend, coworker, etc.) that he/she is trying to quit smoking in the next 30 days - Not smoke more cigarettes than the average of those smoked the previous week - Leave a third of the cigarette without smoking - Refuse cigarette offers

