### Statistical analysis

All data analysis will follow the intention-to-treat principle. This conservative approach aims to minimize selection bias through the inclusion in the primary analysis of data from all the participants randomized to each group, including those who drop out of the study.

We will conduct descriptive analysis to summarize the characteristics of the total sample, and the characteristics of the participants in each of the three groups. The main analysis will be a comparison between both active groups and the control group of the proportions of abstinent smokers at the end of treatment, and between BA intervention group and standard intervention group at the end of treatment, and at 3-, 6-, and 12-month follow-ups, through chi-square tests and odds ratios with 95% confidence intervals. A *t*-test analyses will be conducted to determine whether there were any significant differences between the two active treatment groups and the control group in continuous variables such as BDI-II score. We also will conduct mediation analysis, multiple regression analysis, repeated measures ANOVA, and survival analysis.

The study results will be reported in accordance with the Consolidated Standards of Reporting Trials (CONSORT) 2010 statements [58, 59] and Standard Protocol Item: Recommendations for Interventional Trials (SPIRIT) guidelines [60, 61].

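### Missing the first treatment session is an exclusion criterion, yet that session follows randomisation; this contradicts the rule that everyone randomised is analysed, and it can reach only the active arms.

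*Protocol article*

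**What the plan says.** Three parts of the protocol article bear on this.

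- **Target population, blinding, randomization, and procedure.** The last exclusion criterion is "or failing to attend the first treatment session". On sequence, the section says of the two baseline sessions: "Researchers conducting such assessments will be blind to group allocation, which will occur subsequently". It then describes the 2:2:1 randomisation and continues: "After that, both active treatments will be administered in eight weekly 60-min sessions". It also counts participants who cannot be located as smokers.
- **Treatment delayed control group.** "It will be a delayed-treatment control group for a period of 3 months". These participants are reassessed after the three months and only then offered treatment.
- **Statistical analysis.** "All data analysis will follow the intention-to-treat principle", explained as "inclusion in the primary analysis of data from all the participants randomized to each group, including those who drop out of the study". The main analysis contains a "comparison between both active groups and the control group of the proportions of abstinent smokers at the end of treatment", and a comparison of the two active arms at end of treatment and at each follow-up.

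**The concern.** An eligibility criterion should be settled before allocation. This one cannot be, because session 1 is the first of the eight sessions given after randomisation. Whoever builds the analysis set therefore faces two instructions that cannot both be followed for a person who is randomised and never starts.

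The choice has consequences. Non-starters are likely to be counted as smokers if kept, so leaving them out raises the quit rate of any arm they are taken from. The delayed-treatment arm has no treatment session before its three-month reassessment, so nobody can leave it by this route, and the active-versus-control comparison would be tilted one way. The comparison of behavioral activation with standard treatment, on which both aims and the sample size rest, would lose the protection of randomisation if starting treatment depended on arm. A conflict left open could also be settled after results are known.

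**Working it through.** **1. Order of events.** Baseline assessments, then allocation, then session 1 (all from the procedure section). Non-attendance at session 1 is therefore a post-randomisation event. The baseline visits are called assessment sessions, so the first treatment session cannot mean one of those.

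**2. The two rules for a randomised non-starter.**

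| Rule | Active arm | Control arm |
|---|---|---|
| Exclusion criterion | out | cannot apply before the 3-month reassessment |
| Statistical analysis section | in | in |

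**3. The plan's own figure.** The stated size is 102 per active group for a 20-point difference, 80% power and p = 0.05. The pair of rates and the sidedness are not stated; I assume two-sided. For 28% vs 48%, the continuity-corrected formula gives 102. Fisher's exact test at 102 per arm has power 0.81 for 28% vs 48% and 0.80 for 40% vs 60%. The figure reproduces, so the sample size calculation is not the error.

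**4. Effect on active-arm abstinence.** Let d be the proportion of an active arm that never starts. The protocol gives none, so d is assumed. With non-starters counted as smokers:

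all-randomised rate = starters' rate × (1 − d), so excluding them multiplies the rate by 1/(1 − d).

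| d | All-randomised rate | Rate reported if non-starters are excluded |
|---|---|---|
| 5% | 0.45 × 0.95 = 42.8% | 45% |
| 10% | 0.45 × 0.90 = 40.5% | 45% |
| 20% | 0.45 × 0.80 = 36.0% | 45% |

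**5. Against control.** Take 28% among starters (the low end of the protocol's range) and an assumed control rate of 5%. The starters-only difference is 28 − 5 = 23 points. Counting everyone randomised:

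- d = 5%: 26.6 − 5 = 21.6 points
- d = 10%: 25.2 − 5 = 20.2 points
- d = 20%: 22.4 − 5 = 17.4 points

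The odds ratio is 7.39 for starters only, against 6.89, 6.40 and 5.48.

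**6. Behavioral activation vs standard, no true difference.** Assume 45% all-randomised abstinence in both arms and 102 randomised per arm. Each arm keeps 102 × (1 − d) people with rate 0.45/(1 − d). Exact rejection probability of the two-sided 5% chi-square test without continuity correction:

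| Non-start, one arm vs other | n analysed | Rates among starters | False-positive rate |
|---|---|---|---|
| 10% vs 10% | 92 vs 92 | 50.0% vs 50.0% | 4.6% |
| 10% vs 5% | 92 vs 97 | 50.0% vs 47.4% | 6.4% |
| 15% vs 5% | 87 vs 97 | 52.9% vs 47.4% | 11.7% |

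With continuity correction, the last two rows become 4.7% and 9.1%.

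**7. Power with everyone kept.** Equal d in both active arms, 102 per arm, pooled normal approximation:

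| Starters' rates | d = 0 | 5% | 10% | 20% |
|---|---|---|---|---|
| 40% vs 60% | 0.82 | 0.78 | 0.74 | 0.65 |
| 28% vs 48% | 0.84 | 0.81 | 0.78 | 0.70 |

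**The case against.** The strongest reply is that the only explicit rule on the analysis population includes everyone randomised, while the exclusion list governs sample selection. A reader might infer that the planned analysis discards randomised non-starters. The protocol does not say that, and its analysis section says the opposite. This part of the reply stands: what the text establishes is a contradiction, and the bias follows only if the exclusion is applied.

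A reader might also infer that the main comparison is seriously biased, with a false-positive rate near 12%. That needs a threefold imbalance in non-start, 15% vs 5%, for which the protocol gives no support. Table 2 gives the two active arms the same session 1 content, and behavioral activation material first appears in session 3. The text does not say whether participants learn which active treatment they have before session 1. With equal non-start the error rate stays at about 5%. This objection stands too: bias between the active arms is possible but uncertain.

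Against control the effect is one-directional, but it is unlikely to reverse a large advantage, and that contrast is not among the stated aims. Fig. 1 is not available here and might show where the exclusion falls, which limits certainty. None of this reconciles the two rules in the running text. Nor is this a detail left to a fuller document, since two stated rules conflict.

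**Conclusion.** The point holds as an internal contradiction that must be resolved: the treatment of randomised non-starters is undetermined for every primary outcome. If the exclusion is applied, active-arm abstinence is inflated by about 1/(1 − d) with control unchanged: 2.2, 4.5 and 9 points at d = 5%, 10% and 20% when the reported rate is 45%. This rests on assumed values of d and on non-starters all counting as smokers; any who are followed up and found abstinent would reduce it. For behavioral activation vs standard treatment, the false-positive rate runs from about 5% with equal non-start to 6.4% at 10% vs 5% and 11.7% at 15% vs 5%. The last figure illustrates a large imbalance and is not an expectation.

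**What to change.** - Delete non-attendance at session 1 from the exclusion criteria, or state that it applies only before allocation and removes no randomised participant.
- Analyse everyone randomised in the allocated arm, with non-starters who lack outcome data counted under the existing smoker rule.
- Recruitment is ongoing, so restore to the analysis any randomised participant already removed under this criterion.
- Report an analysis restricted to those who started treatment only as a labelled sensitivity analysis.

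The cost is a one-line amendment with no added assessments. Reported quit rates become somewhat lower, and power among all randomised falls as shown above, for example from 0.82 to 0.74 for 40% vs 60% at an assumed 10% non-start.

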### Sample size and power analysis

Previous studies of cognitive behavioral interventions for smoking cessation [20, 33] and studies of cognitive behavioral interventions for smoking cessation with components targeting depressive symptoms [24, 31] suggest that quit rates after treatment may range between 28% and 61.9%. The sample size for this study was calculated using G*Power3 Software [34]. To detect a 20% difference between the two active groups in the proportion of individuals with tobacco abstinence after treatment, with a power of 80% and a significant *p*-value of 0.05, a total of 102 participants per active group will be required. The sample size of the delayed-treatment control group will be 51 participants. We have chosen an unbalanced design because larger abstinence rates are expected in both active groups as compared to the delayed-treatment control group.

